### Sample size

Using the estimates from the study by Khalid et al. [13], the intervention will increase the incidence of efficacy of treatment for keloid scarring from 45% in the excision followed by radiation group to 70% in the excision followed by intralesional triamcinolone acetonide and 5-fluorouracil group. We calculated that a total of 150 patients (75 in each group) would provide 80% power with a two-sided significance level of 5% to detect this difference between the groups. This allows for 10% non-compliance.

### Composite primary outcome

The primary outcomes are:Reduction in the amount of keloid formation after the intervention in patients with a previous history of keloid caesarean scarChanges in the appearance and specification of the keloid scar after the intervention.

The baseline information including measurement of the scar will be collected at the time of consent and/or around 36 weeks when the patient is consented for the surgery. The scar will be photographed and measured for length and width in millimetres; elevation, hardness and erythema will be graded by the assessor on a 3-point scale (0 = none, 1 = partial, 2 = along entire scar). A subjective symptom score will be graded by the patient for pruritus, pain and swelling on a 3-point scale (0 = none, 1 = occasionally, 2 = all the time).

### Secondary outcomes

The secondary outcomes are:Percentage of women with depression, anxiety and stressPatients’ satisfaction with the treatment and changes in their keloid scars.

### Outcome measures

#### Data collection sheet

A purposefully designed questionnaire consisting of two sections will be used to collect demographics (including age, country of birth, ethnic background, weight, height, BMI, number of previous vaginal births and/or caesarean sections, number of previous miscarriages, abortion and stillbirth, family history of keloid scars, history of any previous surgery and keloid scar on another site of body, gestational age at the time of baseline assessment) and any prior treatment of the keloid scar (section 1) and data on the keloid scar (section 2) including redness, hardness and elevation of the scar compared to the surrounding skin (0 = none, 1 = partially, 2 = entire scar). This section of the questionnaire also enquires about subjective symptoms of the scar including, but not limited to, itching, pain and swelling (0 = none, 1 = occasionally, 2 = all the time). The scar will be measured in millimetres using a hardened stainless steel 150mm Digital Vernier Caliper (Kincrome Pty Ltd, Scoresby, Australia) with a liquid-crystal display (LCD) screen to read an accurate measure to the nearest 0.02 mm. We will also take photographs of the scar to compare the visual changes. Section 2 of the questionnaire will be used at follow-up visits to collect data on the changes in the keloid scar. The same 150mm Digital Vernier Caliper will be used at follow-up visits, and the scars will be photographed again. To improve the objective validity of the trial and minimise recall bias of patients in the symptom scores, the participants will be shown photographs of the scar both before and one year after the intervention. They will be asked if they see any improvement before and after participating in the trial, both before and after seeing their scar photographs. In addition, the participants will assess and grade their satisfaction with the treatment on a 4-point scale (0 = no improvement/poor, 1 = fair, 2 = good, 3 = excellent). The participants will be queried on their overall satisfaction with the treatment (5 = very satisfied, 4 = slightly satisfied, 3 = neutral satisfaction, 2 = slightly unsatisfied, 1 = very unsatisfied). They will also be asked if they think they were in the intervention arm or the control arm of the trial before revealing this information to them at the final visit.

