## Background

Keloid scars affect 10–15% of all wounds and represent an exaggerated healing response that poses a challenge for physicians. They can appear anywhere on the body and can last for years after the initial injury [1]. Patients at risk of keloid scars are usually younger than 30 years and have darker skin. Darkly pigmented skin is the primary risk factor for keloids, which has a 15–20 fold increased risk due to melanocyte-stimulating hormone anomalies. Black, Hispanic and Asian persons are more likely to develop keloid scars than Caucasians. Keloid scars are more than just disfiguring cosmetically; many are also pruritic and painful. They also often result in severe emotional distress [2].

Keloid scars are associated with deteriorated mental health during the post-natal period and can contribute to negative body image, impaired intimate relationships and symptoms of depression. Patients with keloid scars have been reported to be unhappy with their scars due to their perceived stigma and psychological association [3–6]. Consequently, this can result in these patients being unsociable and may interfere with their communication skills, personal relationships and work, life and leisure activities. Patients are usually concerned about the diagnosis and persistent nature of the scars and report that non-empathic management by general physicians and frustrations of current treatment compound their distress [6].

Any kind of trauma that can reach the reticular dermis and cause cutaneous injury (such as insect bites, burns, surgery, vaccinations, skin piercings, acne, folliculitis, etc.) can create abnormal wound healing and trigger keloid scar formation in predisposed people. The abnormal wound healing is described by continuous and histologically localised inflammation and increased inflammatory cells, which result in the increase of fibroblasts, proinflammatory factors, newly made blood vessels and collagen deposits. These changes can stimulate chronic inflammation, which in turn causes the invasive growth of keloid scars. In addition, the upregulation of proinflammatory factors in pathological scars suggests that keloid scars are inflammatory conditions of the reticular dermis of the skin [7, 8].

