Based on the cellular mechanism of keloid formation, one of the first-line options to treat keloid scars is corticosteroid injection into the affected area. The steroids have both direct anti-inflammatory and vasoconstrictive effects. Administration of corticosteroids results in the whitening of keloid scars, suggesting a decrease of blood flow in the scar due to vasoconstriction [7].

Another suggested treatment of keloid scars is surgical removal of the scar. However, since surgical removal of the keloid usually only provides temporary cosmetic relief and invariability followed by even more aggressive regrowth of scar tissue in 50–100% of cases, many clinicians perform surgical excision of the keloid scar followed by sub-dermal corticosteroid injections. This has been suggested to be effective for patients with small or single site lesions [9].

Some studies have used immediate wound edge corticosteroid injection after the excision in patients with hypertrophic scars and keloid scars, followed by regular injection of corticosteroid: usually a weekly injection for 2–5 weeks followed by monthly injections for 3–6 months [10]. This combination of surgical removal and corticosteroid injections has been shown to improve outcome. This dose of steroid is substantially more than the stat dose we plan to use in our study and requires multiple visits and repeated injections.

A thorough literature search has shown a lack of research on the surgical excision and injection of corticosteroid injection immediately after the excision of the existing caesarean section keloid scars. Therefore, in the proposed study, we aim to investigate the effect of corticosteroid (triamcinolone acetonide) injection immediately after surgical removal of old caesarean section keloid scars on the recurrence of the scars.

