### Data analysis

Intention-to-treat analysis will be performed using SPSS Advanced Statistics version 24.0 (SPSS, Chicago, IL, USA). Descriptive statistics will be used to summarise the demographic data; binary outcomes will be summarised with a relative risk (RR) and 95% confidence intervals (CIs) and compared between the two groups using a χ^2^ test (or Fisher’s exact test where applicable). Comparison of the number of patients with keloid formations within groups and between the two groups will be done using a χ^2^ test. A *t* test will be used to assess continuous non-skewed variables; these will be presented as means with standard deviations. For skewed ordinal data, the Mann–Whitney *U* test will be used; these data will be presented as medians with interquartile ranges. Difference in the effect over the sub-groups will be assessed using logistic regression. Outcomes of interest will be number of patients with keloid formation, changes in the appearance and specification of the keloid scar, depression, anxiety, stress and patient’s satisfaction. Changes in the appearance and specification of the keloid scar after the intervention will be summarised into two groups (binary outcome: 0 = changed, 1 = not changed) and will be analysed using logistic regression adjusting for the number of keloids formed and demographic variables. A *p* < 0.05 will be considered statistically significant.

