## Discussion

Keloid formation often can be prevented or reduced if anticipated with immediate therapy. Once established, keloids are more difficult to treat, with a high recurrence rate regardless of treatment. Corticosteroids are a commonly used and effective treatment for established keloids on wounds in other area [16–18]. Corticosteroids suppress inflammation by inhibiting fibroblasts and mitosis while increasing vasoconstriction in the scar [19, 20]. Their effectiveness and side effects in subsequent caesarean section for those with established keloids has not been established. Yet caesarean section is easily the most common operation done, and keloid formation in these young women of childbearing age can be very distressing [3, 6, 21–23].

Other treatment modalities have also been used for keloid scars after caesarean section. Radiation therapy has been used with some clinical success [24, 25]. However, this modality of treatment requires multiple visits for radiation therapy during the post-natal period when more time is needed to care for the newborn. Our mode of treatment with a single administration of triamcinolone acetonide takes into consideration the need of the mother to have time to care for her newborn.

Common adverse effects of triamcinolone acetonide include atrophy, telangiectasia and hypopigmentation [26]. Steroids have been implicated as an aetiology in delayed wound healing. Although there is evidence in the literature that steroids delay wound healing, most studies are performed in vitro or use high systemic doses. Although wound disruptions have occurred in patients taking corticosteroids [26], treatment doses are generally below the level required for inhibition of wound healing in clinical practice. Acute, high-dose systemic corticosteroid use likely has no clinically significant effect on wound healing [27]. There is a retrospective evaluation study of post-operative intralesion steroid injections on wound healing [28]. Overall, there was not a statistically significant difference between the steroid groups and the non-steroid group. Therefore, one-time post-operative intralesion steroid injections were not found to delay wound healing [28].

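### The graded scar items cannot tell a lighter or depressed scar from normal skin, so the appearance part of the primary outcome may favour the injection by an unknown amount

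*Protocol article*

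**What the plan says.** The protocol article describes the assessor's grading twice. The Data collection sheet section lists "redness, hardness and elevation of the scar compared to the surrounding skin (0 = none, 1 = partially, 2 = entire scar". The Composite primary outcome section gives the same three features: "elevation, hardness and erythema will be graded by the assessor on a 3-point scale (0 = none, 1 = partial, 2 = along entire scar". The Secondary objectives section uses the same features, together with patient discomfort, to explain what it means by the specification of the scar.

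These grades feed the second component of the primary outcome. According to the Data analysis section, this component "will be summarised into two groups (binary outcome: 0 = changed, 1 = not changed". It plans a logistic regression on that binary variable.

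On the drug, the Discussion states: "Common adverse effects of triamcinolone acetonide include atrophy, telangiectasia and hypopigmentation". Under Procedures, only the intervention arm is injected. The control arm has excision alone.

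Other information on the scar is collected. "The scar will be photographed and measured for length and width in millimetres", and women grade itching, pain and swelling, say whether they see improvement, and rate their satisfaction. The Follow-up section has late side effects of the injection assessed at 6 weeks, 6 months and 12 months.

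**The concern.** Each assessor item measures an excess over surrounding skin and stops at none. Colour is represented only by redness and contour only by elevation. Two effects that the protocol itself calls common for the study drug lie on the other side of that floor. Hypopigmentation makes a scar lighter than its surroundings, and atrophy can leave it lower. The form gives such a scar the same mark on the affected item as skin that has healed normally.

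Because the drug is given in one arm, effects that it causes fall in that arm. The trial could then report a better appearance after injection when part of the difference is a visible drug effect that the items cannot register. An analysis plan written later cannot restore an item that was not recorded at the visits, except so far as the photographs allow. The Trial status section puts the start of recruitment in May 2019.

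**Working it through.** **What the items can register.** The table applies the stated 0–2 scale to possible states of the new scar. A dash means that the state does not determine the item.

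| State compared with surrounding skin | Redness | Elevation | Hardness |
|---|---|---|---|
| Same as surrounding skin | 0 | 0 | 0 |
| Red and raised along its whole length | 2 | 2 | – |
| Lighter (hypopigmented) | 0 | – | – |
| Depressed (atrophic) | – | 0 | – |
| Telangiectasia | 1 or 2 possible | – | – |

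Rows three and four match row one on the affected item. Row five goes the other way, since visible vessels could be graded as redness and would count against the injection.

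**What the analysis does with them.** A scar that was red and raised at baseline and is pale and sunken at 12 months is changed. So is one that has become normal, and so is one that has become worse. The binary code separates none of these, so it does not repair the items.

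**Whether other data close the gap.** Length and width do not measure colour or depression. Photographs are taken for visual comparison, but no assessor grading of colour or contour from them is described. Satisfaction is a secondary outcome. Side effects are a secondary objective, but they are not in the list under Secondary outcomes or among the outcomes of interest in the Data analysis section. Nothing ties any of these to the appearance result.

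**Size.** The plan has no figure on this point. Its sample size is not affected and can be reproduced. For 45% against 70%, two-sided 5% and 80% power, the usual formula gives 61 per arm, or 68 with continuity correction. 68 × 1.10 = 74.8, so 75 per arm and 150 in total.

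No rate of hypopigmentation or atrophy is given for a single injection, so the following is an illustration under assumptions, not an estimate. Suppose that appearance is scored as improved or not, that 45% of scars are truly improved in both arms, and that a further *a* percentage points of injected scars count as improved only because pallor or depression goes unseen. The 45% is borrowed from the Sample size section, where it refers to treatment efficacy and not to appearance. With n = 75 per arm, p₁ = 0.45, p₂ = 0.45 + *a* and p̄ their mean, the chance of a significant result favouring the injection is about

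Φ{[*a* − 1.96 √(2p̄(1 − p̄)/n)] / √([p₁(1 − p₁) + p₂(1 − p₂)]/n)}.

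For *a* = 0.10: p̄ = 0.50, the first root is 0.0816 and the second 0.0812. (0.10 − 0.1600)/0.0812 = −0.74, so Φ = 0.23.

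| *a* (points) | Women of 75 | Chance of a significant result |
|---|---|---|
| 5 | 3.75 | 9% |
| 10 | 7.5 | 23% |
| 15 | 11.25 | 45% |
| 20 | 15 | 70% |

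Here *a* counts only women who would otherwise not be improved. The rate of pale or depressed scars could be higher than *a*, because some of those scars would have flattened and softened anyway.

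**The case against.** The strongest reply is that efficacy and harm are kept apart on purpose. The primary objective concerns keloid formation, a flat scar is rightly not a raised keloid, and drug effects are assessed separately at every follow-up visit. Women also compare photographs and can say that they dislike a pale or sunken scar. The article condenses a longer protocol, and the word before the item list does not say that the list is closed. Much of this stands: the changes are partly captured, and separate reporting is a legitimate choice. But three sections name the same assessor features, and none adds pallor or depression. Appearance is also itself a primary component, and its stated grades cannot show whether a change is a good one.

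A reader might infer more than the documents support, in four ways:

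- **That such a scar gets the best grade overall.** The 0 applies to the affected item only. A hypopigmented scar may still be hard, raised, long or wide.
- **That the direction of bias is established.** The coding has no direction, no section defines improvement, and telangiectasia could count against the injection.
- **That the Background supports the point where it says** "Administration of corticosteroids results in the whitening of keloid scars". It attributes this to reduced blood flow and does not describe pigment loss or an adverse effect.
- **That the effect is largest in the main risk group.** The Background says "Darkly pigmented skin is the primary risk factor for keloids". It does not say that hypopigmentation shows most on dark skin, plausible as that is.

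The Background also describes the planned single dose as substantially lower than earlier repeated regimens, so the word common in the Discussion need not carry over at the same rate. No rate of pale or depressed scars after excision alone is given either.

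**Conclusion.** The concern holds in a limited form. On the colour and contour items as stated, a lighter or depressed scar cannot be told from normal skin. The protocol names both states as common effects of a drug given in one arm only, and the undirected coding of the appearance outcome does not correct for this. The comparison may therefore favour the injection.

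The documents do not show that it does, or by how much. The conclusion rests on the item list being as the three sections give it, and on these effects occurring at some rate after one injection. The percentages in the working depend on assumed rates and must not be read as the expected bias. This is a worthwhile and inexpensive improvement, not a flaw that invalidates the trial.

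**What to change.** In section 2 of the data collection sheet, at baseline and every follow-up visit and in both arms, have the same blinded assessor also grade:

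- colour against surrounding skin: same, redder, lighter or darker;
- contour: level, raised or depressed;

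each with the existing 0–2 extent.

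In the Data analysis section, replace changed versus not changed with improved versus not improved. Report the number of lighter or depressed scars by arm next to the appearance result. Add a sensitivity analysis in which a lighter or depressed scar does not count as improved on the affected item.

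The primary definition should not go further and let any pale or depressed segment rule out improvement. The old scar is excised, so every segment of the new one is new, and such a rule would let a small pale area cancel a real reduction in keloid.

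The cost is two extra items at visits already planned, and an apparent benefit that may come out smaller. For women already seen, the photographs may allow part of the grading to be done afterwards.

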### Participants

The inclusion criteria for the study are (1) age between18–45 years old; (2) being pregnant at the time of recruitment; (3) presence of a keloid scar from a previous caesarean section; (4) planned caesarean section for the current pregnancy. Women of all ethnicities with a keloid scar following a previous caesarean section will be eligible to participate in the study.

The exclusion criteria for the study are (1) being primigravida and (2) having a previous caesarean section with no keloid scar. Since the aim of the study is to investigate the impact of treatment on the caesarean section keloid scar, the type of skin excision in the caesarean section (vertical or horizontal) will not be an inclusion/exclusion criterion.

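### Scar length, part of the second primary outcome, is to be read on a rigid 150 mm caliper, which caps a single straight reading and reads curved scars short

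*Protocol article*

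**What the plan says.** Under Participants, the size criterion is only "presence of a keloid scar from a previous caesarean section", and "the type of skin excision in the caesarean section (vertical or horizontal) will not be an inclusion/exclusion criterion". No upper limit on scar length is set.

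Under Composite primary outcome, "The scar will be photographed and measured for length and width in millimetres", next to 3-point grades for elevation, hardness and erythema and a patient-graded symptom score. Baseline is taken in pregnancy, "at the time of consent and/or around 36 weeks when the patient is consented for the surgery".

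The Data collection sheet section fixes the instrument: "The scar will be measured in millimetres using a hardened stainless steel 150mm Digital Vernier Caliper", with a display "to read an accurate measure to the nearest 0.02 mm". It adds: "The same 150mm Digital Vernier Caliper will be used at follow-up visits". Photographs are taken for visual comparison. They are not described as a way to obtain length.

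The Follow-up section places later assessments at 6 weeks, 6 months and 12 months and has one researcher take every measurement. The Blinding section says the outcome assessor does not know the allocation. Data analysis reduces change in appearance and specification to a binary variable, changed or not changed.

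**The concern.** The instrument suits scar width but not every scar length that the eligibility criteria admit. There are two separate limits.

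- **Range.** A single end-to-end reading stops at 150 mm. A scar whose ends lie further apart has to be capped, left missing or pieced together. If a baseline is capped, later shortening at the top of the range is partly hidden.
- **Geometry.** Rigid jaws span the straight line between the two ends. A scar that curves, or that lies on a convex abdomen, is longer along the skin than that line. This applies below 150 mm as well.

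The second limit would matter less if the shortfall were constant within a woman. Baseline, however, is measured on a pregnant abdomen and follow-up on a post-partum one. If the curvature differs, part of the recorded change in length reflects body shape and not the scar. Length is one component of the second primary outcome, and a few millimetres of artefact could move a woman between changed and not changed.

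**Working it through.** **Inputs from the article.** Caliper range 150 mm; display resolution 0.02 mm; 150 women planned (Sample size). The article gives no scar length, spread or curvature, so it has no figure of its own on this point to reproduce.

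**Assumed inputs.** Scar length L along the skin of 120 or 150 mm; radius of curvature R of 100, 150, 200 or 300 mm; for the range question, normally distributed lengths with SD 20 mm and means from 100 to 150 mm.

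**1. Chord against true length.** A straight caliper on an arc reads 2R·sin(L/2R). For L = 150 mm and R = 150 mm this is 300 × sin(0.5) = 143.8 mm.

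| R (mm) | Reading, L = 150 | Short by | Reading, L = 120 | Short by |
|---|---|---|---|---|
| 100 | 136.3 | 13.7 (9.1%) | 112.9 | 7.1 (5.9%) |
| 150 | 143.8 | 6.2 (4.1%) | 116.8 | 3.2 (2.6%) |
| 200 | 146.5 | 3.5 (2.3%) | 118.2 | 1.8 (1.5%) |
| 300 | 148.4 | 1.6 (1.0%) | 119.2 | 0.8 (0.7%) |

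The shortfalls of 0.8 to 13.7 mm are 0.8/0.02 = 40 to 13.7/0.02 = 685 times the display resolution. That resolution therefore says little about the accuracy of a length reading.

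**2. Apparent change from baseline to follow-up.** Take a length of 150 mm along the skin at both visits. If R = 150 mm at baseline and 300 mm at follow-up, the readings are 143.8 and 148.4 mm, an apparent lengthening of 4.6 mm. With the radii reversed it is an apparent shortening of 4.6 mm. The documents do not show which direction applies, or whether the change is this large.

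**3. Share beyond 150 mm along the skin.** P(L > 150) = 1 − Φ((150 − mean)/20).

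| Mean (mm) | Share | Of 150 women |
|---|---|---|
| 100 | 0.6% | about 1 |
| 110 | 2.3% | about 3 |
| 120 | 6.7% | about 10 |
| 130 | 15.9% | about 24 |
| 140 | 30.9% | about 46 |
| 150 | 50.0% | 75 |

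**4. The two limits partly offset each other.** Because the jaws span the chord, the longest arc that still fits is 2R·arcsin(150/2R): 169.6, 157.1, 153.8 and 151.6 mm at R = 100, 150, 200 and 300 mm. At a mean of 140 mm the share out of reach falls from 30.9% to 1 − Φ((169.6 − 140)/20) = about 7% (10 women) at R = 100 mm, and to 1 − Φ((157.1 − 140)/20) = about 20% (29 women) at R = 150 mm. Scars that escape the cap in this way are the ones read shortest.

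**The case against.** Five points can be made for the plan as written.

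- **The share affected is not shown.** This stands. A reader might infer that a large fraction of women fall outside the caliper's range. The documents give no lengths, and the assumed range runs from almost none to half. They also do not say that the measured keloid spans the whole incision.
- **Scars over 150 mm can be measured.** This largely stands. A reader might infer that they cannot be measured at all. The limit is on one straight reading: a curved scar somewhat over 150 mm can fit the jaws, and a longer one could be read in segments.
- **The comparison between arms is protected.** This stands. A reader might infer bias towards one treatment. The same caliper and the same blinded researcher serve both arms, and the passage from pregnancy to post-partum is common to both, so the error should on average be similar between them.
- **Length has a limited role.** This stands. Keloid formation is analysed as a number of patients and the sample size rests on a proportion; neither is stated to depend on length. Within the second primary outcome, length is one item among several. Width and the 3-point grades are little affected.
- **Technique belongs in the full protocol.** This stands in part. The absence of a rule for segments or posture in a condensed article is not counted here. The choice of instrument is different, because the article states it down to model range and resolution and applies it to follow-up as well.

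**Conclusion.** The point holds as a measurement weakness in one component of the second primary outcome. The article fixes a rigid 150 mm caliper for scars of unlimited length and either orientation. A single reading is capped at 150 mm end to end and understates the length of a curved scar. Under assumed radii of 100 to 300 mm the understatement for a 150 mm scar is 13.7 to 1.6 mm, and a change in radius from 150 to 300 mm would produce 4.6 mm of apparent change. The number of women beyond range is unknown.

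The harm is added noise and distorted change from baseline, carried into a changed/not changed classification. How many women would be reclassified cannot be computed, because the article gives no threshold for change. The documents do not support a claim of bias between arms, of scars that are impossible to measure, or of a known large share affected. Priority is minor to moderate.

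**What to change.** In the Data collection sheet section, specify that scar length is measured with a flexible tape laid along the scar, to the nearest millimetre and in the same posture at every visit. Keep the digital caliper for width, where its range and resolution are suitable.

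Trial status says recruitment began in May 2019, so some baselines may already be caliper readings. For those women, caliper length should also be recorded at each follow-up, so that every woman's change is computed with one method. A baseline length cannot be retaken once the keloid has been excised, so the change is best made promptly.

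The cost is a disposable tape and a few changed sentences. There are three downsides: coarser nominal resolution for length, which is unimportant beside the chord error; a period with two methods in use; and any real difference in skin length between late pregnancy and post-partum, which a tape does not remove.
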